**V. Justification**

We propose a placebo-controlled trial to examine the effect of daily folic acid supplementation on efficacy of SP in reducing peripheral parasitemia in pregnant women in western Kenya. Folic acid supplementation is part of recommended care for pregnant women in Kenya. IPT with SP is the Kenya national policy for the control of malaria in pregnancy. However, data exist that suggest that folic acid supplementation in combination with SP treatment for malaria impairs clearance of parasitemia in children. It is therefore important to determine if concomitant folic acid supplementation reduces the efficacy of SP in clearance of *P. falciparum* parasitemia in pregnant women, and if delaying of the intake of folic acid tablets for 2 weeks following an SP treatment dose or reducing the folic acid dose may be a safe alternative. It is important to note that all study women will receive folate supplementation, but in two groups it will be continued when SP is given, while in the other group folate supplementation will be suspended for 2 weeks following the SP treatment dose. Although the Kenya national recommendation is to start folic acid supplementation two days after SP is taken, we are concerned that two days may not be sufficient, given the long half-life of SP.

If concomitant folic acid supplementation (either 5 mg or 400 microgram) is found to impair the efficacy of SP treatment in pregnant women, this will have implications for the Kenya national malaria control guidelines as well as all countries in malaria-endemic areas where IPT with SP during pregnancy is recommended. In Kenya, pending on the results of this study, the delay of folic acid intake after treatment with SP may need to be changed from two days to two weeks or the dose of folic acid may need to be reduced when it is given in combination with SP.

**VI. Objectives**

The purpose of this study is to assess in pregnant women

1. If concomitant folic acid supplementation affects the efficacy of SP in clearance of maternal *P. falciparum* peripheral parasitemia, and improving hemoglobin levels.

2. If SP is still efficacious in treatment of malaria parasitemia in pregnant women in an urban area where SP has been used as first line treatment and for IPT in the past three years.

Secondary objective:

- 1. If HIV infection status affects SP efficacy in clearance of maternal *P. falciparum* peripheral parasitemia.

**VII. Design and Methodology**

**A. Study sites**

This study will be conducted at Nyanza Provincial General Hospital (NPGH), Bondo District Hospital (BDH) and Siaya District Hospital (SDH).

NPGH is a government hospital in Kisumu. Kisumu is located on the shores of Lake Victoria in western Kenya and has about 300 000 inhabitants. Nyanza Provincial General Hospital has been the Ministry of Health site of other CDC/KEMRI studies, including a previous study to assess the safety and efficacy of intermittent SP in the reduction of placental malaria in pregnant women and a study to examine the interaction between malaria in pregnancy and HIV infection. HIV seroprevalence among pregnant women participating in the previous study was 25% and malaria prevalence in the third trimester was 20.1%. This was, however, a selected group of women in their third trimester with uncomplicated pregnancies; women who were excluded may have been more likely to be parasitemic, and women in their second trimester are more likely to be parasitemic compared to women in their third trimester. We expect the malaria prevalence in this ANC population to be higher than 20.1%. Sentinel surveillance in the same hospital has reported an HIV prevalence of 33% among pregnant women (Glynn et al, 2000).

Bondo and Siaya are both located approximately 70 km from Kisumu, in Western Kenya. Bondo has a population of about 30 000 inhabitants (Kenya Malaria Information Service, District Population Projections). BDH is a 42-bed facility, serving the local low-income population. Approximately 400 women attend the ANC per month and one third of them do so for the first time. BDH has collaborated in other CDC/KEMRI studies previously, including a randomized controlled trial of the efficacy of bednets in reducing all cause mortality in Rarieda Division, a nearby area.

The antenatal clinic in SDH sees approximately the same number of women as in Bondo. Siaya hospital is the site where at present a study is conducted assessing the efficacy of treatment with SP among adults with known HIV-status.

In all sites, HIV-counseling and testing is provided in the ANC as part of a program to provide nevirapine to HIV-seropositive pregnant women during delivery to reduce vertical transmission of HIV. In addition, the study clinic employs experienced counselors who can assist with counseling. CDC/KEMRI hospital staffs have been trained to conduct interviews of patients, and to collect and properly handle laboratory samples. The main CDC/KEMRI laboratories are located in Kisian, 10 kilometers from Kisumu.

**B. Design**

We propose a study to look at the interaction between folic acid supplementation and intermittent treatment with SP for malaria in pregnancy in an area where both HIV infection and malaria are common.

We will use a randomized double blind placebo-controlled design, where by pregnant women with peripheral parasitemia will be at random allocated to receive one of three treatment options:

Arm 1: 3 tablets of SP and daily folic acid, 5 mg, according to the national policy (SP/FA5)

Arm 2: 3 tablets of SP and daily folic acid, 400 g, according to international recommendations, to be replaced by folic acid 5 mg after 14 days (SP/FA0.4)

Arm 3: 3 tablets of SP and daily placebo, up to 14 days after the intake of SP, to be replaced by folic acid 5 mg after 14 days (SP/PFA)

Although participating women will be followed up to 28 days after the start of treatment, folic acid 5 mg will be provided until the end of their pregnancy. Women will not be followed further during pregnancy or delivery.

**C. Study population**

All pregnant women who are presenting at the ANC who have not received folate supplementation during the current pregnancy will be eligible for screening for malaria. Only women with a positive blood smear for malaria will be enrolled in the study.

***Criteria for inclusion***

1. Parasitemia with a parasite density of ≥ 500 parasites/microliter
2. Gestational age > 16 weeks and < 35 weeks
3. Willingness to provide blood samples and participate in HIV counseling and testing
4. Available for follow up for the entire study period
5. Hb > 7 g/dl
6. Age 15-45 years

***Criteria for exclusion***

1. Use of folate in the last 4 weeks

2. Gestational age ≤16 weeks or ≥35 weeks

3. History of an allergy to sulphonamides or other unknown drugs

4. An intake of sulpha-containing drugs or 4-aminoquinolones in the previous month

5. A urine test positive for sulfa-compounds

6. Sickle cell disease

7. Concomitant diseases needing treatment with co-trimoxazole or other sulfa-containing drug

8. Hb ≤ 7 g/dl

9. Severe malaria or any other serious medical condition requiring hospitalization and/or additional treatment. Clinical danger signs of severe malaria include prostration, impaired consciousness, respiratory distress, multiple convulsions, circulatory collapse, pulmonary oedema, abnormal bleeding, jaundice, and hemoglobinuria. Laboratory signs of severe malaria include severe anemia (Hb < 7 g/dl), hypoglycemia, acidosis, hyperlactataemia, hyperparasitaemia (a parasitemia > 100,000 parasites/µl), and renal impairment

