The most common side effects reported with quinine therapy include dizziness, decreased hearing, tinnitus, blurred or double vision, photophobia, nausea, and vomiting. Although the US drug labeling categorizes quinine (Merrell Dow) as Category X (contraindicated), the congenital abnormalities reported occurred at abortifacent doses (Briggs et al, 1986). In addition, quinine at therapeutic doses is not felt to induce premature delivery (Looareesuwan et al, 1985). Quinine is recommended as the drug of choice for treatment of uncomplicated and severe malaria during pregnancy, including CDC (http://www.cdc.gov/malaria/diagnosis_treatment/clinicians3.htm), Health Canada (CATMAT: http://www.hc.sc.gc.ca/pphb-dgspsp/publicat.htm) and the WHO (WHO 2001).

The most common potential adverse drug reactions associated with mefloquine include headache, nausea, dizziness, difficulty sleeping, anxiety, vivid dreams, and visual disturbances. Mefloquine treatment can also cause serious side effects, such as seizures, depression, and psychosis. Mefloquine has not been shown to be associated with congenital abnormalities (Phillips-Howard & Wood, 1996; McGready et al 2002). However, one retrospective study from Thailand reported that mefloquine treatment may be associated with an increased rate of stillbirths but no definite conclusions could be drawn (WHO 2001, Nosten et al 1994, 1999). Given this uncertainty, we feel that mefloquine should be used only for women who fail quinine therapy (or who cannot tolerate it). Because malaria can have severe adverse consequences for both mother and fetus, women need treatment for parasitemia during pregnancy and we feel that in women who have failed quinine (who have no other better option), the benefits of mefloquine therapy outweigh the risks. WHO has recommended that mefloquine can be used for treatment of malaria during pregnancy in the 2nd and 3rd trimesters (WHO 2001).

Although amodiaquine is regularly used in Kenya for malaria in pregnancy, and is mentioned as well as a treatment option in the national guidelines (MOH 2002), a recent review exposed the lack of safety data on amodiaquine in pregnancy (Thomas et al, 2004), and for this reason we do not feel it is a good option for treatment of SP treatment failure.

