Does any member in your household own: A bicycle [_] 1=yes 2=no 9=don’t know

A motorcycle [_] 1=yes 2=no 9=don’t know

A car [_] 1=yes 2=no 9=don’t know

Cattle/goats or sheep [_] 1=yes 2=no 9=don’t know

Chicken [_] 1=yes 2=no 9=don’t know

Land [_] 1=yes 2=no 9=don’t know

For the last week, how many people have lived in your household (including the pregnant woman)? [_][_] (99 if unknown)

How many of these were children less than 5 years? [_][_]

How much money did you use in the last week for food? [_]

1 <100 Ksh per week

2 100-200 Ksh per week

3 200-500 Ksh per week

4 500-1000 Ksh per week

5 > 1000 Ksh per week

8 Does not like to answer

9 Does not know

Do you grow vegetables in your own garden? [_] 1=yes 2=no 9=don’t know

MEDICAL/OBSTETRICAL HISTORY

**9.** Number of previous children who were born alive [_][_]

Number of previous children who were born dead (still births) [_][_]

Number of previous abortions [_][_]

Total Number of previous pregnancies [_][_]

Number of previous life born children who are still alive [_][_]

When did your last pregnancy end? [_][_]/[_][_]/[_][_][_][_]

If unknown, how long was this ago (in months)

How did your last pregnancy end? [_]

1=live birth

2=still birth

3=abortion or miscarriage

If live birth, is he still alive now? [_] 1=yes 2=no

If dead, how old was the child when he/she died? [_][_][_]

**10.** No of weeks gestation (ANC) according to palpation today [_][_]

Date of last menstrual period known [_] 1=yes 2=no

If yes, date of first day of last menstrual period [_][_]\[_][_]\[_][_][_][_]

Do you feel the movements of the baby [_] 1=yes 2=no

Did you feel like having fever in the last 7 days? [_] 1=yes 2=no

**11.** Have you been treated for malaria in the past 4 weeks? [_] 1=yes 2=no

If yes, what treatment did you receive? **(Write name drug, number of tablets per day, and number of days)**

________________________________________________________________________

Have you used any of the following drugs in the last 4 weeks?

Folic acid tablets [_] 1=yes 2=no 9=don’t know

Septrin (other names for septrin: look up) [_] 1=yes 2=no 9=don’t know

Metakelfin [_] 1=yes 2=no 9=don’t know

Fansidar (other names for SP: look up) [_] 1=yes 2=no 9=don’t know

Have you ever had an adverse reaction to a drug, like skin rash, jaundice or vomiting?

[_] 1=yes 2=no 9=don’t know

If yes, what drug?

If yes, what reaction? __________________________________________

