Are you currently using any medicine? [_] 1=yes 2=no

If yes: what medicine?

Are you known with any illness on the moment? [_] 1=yes 2=no 9=don’t know

If yes, what illness? ________________________________________________

Are you on the moment

Using treatment for tuberculosis? [_] 1=yes 2=no 9=don’t know

Using treatment for sickle cell disease [_] 1=yes 2=no 9=don’t know

During this pregnancy, have you been admitted in hospital?

[_] 1=yes 2=no 9=don’t know

Date of hospitalization: [_][_]/[_][_]/[_][_][_][_]

If yes, for what problem? ____________________________________________________

**12.** Copy from the ANC card:

Date of the first prenatal visit [_][_]/[_][_]/[_][_][_][_]

Gestational age at first visit (weeks) [_][_] (99 if unknown)

Total number of prenatal visits so far (include this visit) [_][_] (99 if unknown)

Examination:

**13.** Axillary temperature [_][_].[_]oC

**14.** Weight [_][_].[_] kg (without shoes)

**15.** Height [_][_][_] cm (without shoes)

**16.**  Conclusion: [_]

1) Candidate: Randomized into group [_] 1 = group A

2 = group B

3 = group C

2) Excluded: reason:

**17.** Checklist for enrolled women:

Folic acid tablets explained and supervised: [_]

SP tablets supervised: [_]

Iron tablets explained and given: [_]

Follow up appointment and card made [_]

Address form made [_]

Home drive arranged [_]

Staff ___________signature, date

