**______________________________________________________________________________**

**14.** Conclusion: [_] 1) Continue, next appointment: [_][_]/[_][_]/[_][_]

2) Excluded: reason: [_]

3) Dropped out: reason:

4) End of study after 28 days

Reasons for exclusion:

1. Use of other sulfa containing drugs or antimalarials when being in the study.

2. RIII resistance: -A parasite density at Day 3 that is > 25% of the Day 0 parasite density.

3. RII resistance: -Parasites at 7 days and a positive blood smear at day 3 with a parasite density that is < 25% of the Day 0 parasite density.

4. Early RI: -A negative Day 3 blood smear with a positive blood smear on any day between Day 4 and Day 14 or a positive Day 3 blood smear with a parasite density that is < 25% of Day 0, a negative Day 7 blood smear, and a positive blood smear on any day between Day 8 and Day 14.

5. Sensitive or late RI: -A Day 3 parasite density that is <25% of the Day 0 density and negative blood smears on every follow-up examination between Day 7 and Day 14.

6. Other reason, specify_________________________________________________

**In case of clinical or parasitologic failure: treat with Quinine 600 mg TDS for 7 days, and make a new appointment after 7 days.**

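### The entry washout omits quinine, mefloquine and other antimalarials, so clearance begun by one of these drugs may be credited to SP; the effect is probably small and cheap to remove

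*Protocol*

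**What the plan says.** **Entry criteria.** Protocol section VII.C, exclusion 4, is "An intake of sulpha-containing drugs or 4-aminoquinolones in the previous month". The second class is read here as 4-aminoquinolines (chloroquine, amodiaquine). Exclusion 5 adds a laboratory check for one class only: "A urine test positive for sulfa-compounds". Exclusion 9 is "Severe malaria or any other serious medical condition requiring hospitalization and/or additional treatment". Inclusion 1 asks for "Parasitemia with a parasite density of ≥ 500 parasites/microliter".

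**Screening history.** Item 11 of the screening form (Annex 4, SPF-FORM 1a) asks "Have you been treated for malaria in the past 4 weeks", with space for the drug, tablets per day and days. It also asks "Are you currently using any medicine". Section VII.E (Recruitment) has a medication history taken and leaves the enrolment decision to the study physician, who applies the listed criteria.

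**After entry.** The follow-up form (Annex 4, SPF-FORM 2, item 14) gives as its first reason for exclusion "Use of other sulfa containing drugs or antimalarials when being in the study". Section VII.E also asks women not to take antimalarials on their own during follow-up.

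**The drugs not covered.** Section VIII.E states: "Quinine is recommended as the drug of choice for treatment of uncomplicated and severe malaria during pregnancy". The Follow up part of section VII.E names mefloquine as an alternative in the Kenyan government guidelines.

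**The concern.** The washout is there so that what happens to the smear after day 0 can be attributed to SP, with or without folic acid. It does this for two drug classes. A woman part-way through quinine for uncomplicated malaria, with a smear still above the threshold, meets the parasite criterion and breaks no listed exclusion. If she then clears, the earlier drug may be the reason, yet she counts as an SP success.

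Three uses of the data are affected to different degrees:

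- Objective 2 (section VI) asks whether SP still works. It depends on the absolute failure rate, which randomisation does not protect.
- Section F1 calls for a blinded interim analysis if overall failure reaches 50% at 14 days. That is also an absolute rate.
- Objective 1 is a comparison between arms. Here such women mainly dilute the contrast.

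**Working it through.** **1. Can such a woman enter?**

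| Provision | Reaches quinine, mefloquine or another non-listed antimalarial? |
| --- | --- |
| Exclusion 4 | No; sulfa-containing drugs and 4-aminoquinolines only |
| Exclusion 5 (urine test) | No; sulfa compounds only |
| Exclusion 9 | No; needs severe malaria or another serious condition |
| Inclusion 1 (density) | In part; keeps out women already below 500 per microliter, not those still above it |
| Form 1a, item 11 | Records the exposure, but no criterion acts on it outside the two listed classes |
| Form 2, item 14, reason 1 | Yes, but only for use after entry |

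Because enrolment follows the listed criteria, a physician who reads of recent quinine in the history has no listed ground to refuse. The gap is limited to women still at or above the threshold while on such a drug or carrying residual levels of it.

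**2. The plan's own sample size.** Inputs from section VII.D: 5% v 15% parasitological failure at day 7, 80% power, 95% confidence (taken as two-sided 5%), 25% loss, 200 per arm.

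n = [1.96 √(2 p̄(1 − p̄)) + 0.842 √(p1(1 − p1) + p2(1 − p2))]² / (p2 − p1)², with p̄ = 0.10

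= [1.96 × 0.4243 + 0.842 × 0.4183]² / 0.01 ≈ 140.1, so 141 per arm. With continuity correction it is 160, and 160 × 1.25 = 200, which is the stated figure. Loss of 25% from 200 leaves 150 evaluable per arm, with power (no continuity correction) of 82.6%. The stated figure is reproduced and is not in dispute on this point.

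**3. Effect of carry-over.** Let f be the share of each arm with an active non-listed antimalarial, p the failure rate under SP alone and q the failure rate among those women. The observed rate is (1 − f)p + f q.

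- If q = 0, nobody in the group can fail and the observed rate is p(1 − f). For a given f this is the largest possible understatement.
- If q = p, nothing changes.
- If q > p, for example because these women carry infections that an earlier drug failed to clear, failure is overstated.

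If q is the same in both arms, the difference between arms is (1 − f)(p2 − p1) whatever q is. That is dilution without differential bias.

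The protocol gives no value for f. The values below are assumed, with q = 0 and 150 evaluable per arm:

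| f | Failure rates | Difference (points) | Power | A true 50% reads as |
| --- | --- | --- | --- | --- |
| 0 | 15% v 5% | 10.0 | 82.6% | 50% |
| 2% | 14.7% v 4.9% | 9.8 | 81.8% | 49% |
| 5% | 14.25% v 4.75% | 9.5 | 80.4% | 47.5% |
| 10% | 13.5% v 4.5% | 9.0 | 78.0% | 45% |

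At f = 10%, true overall failure would have to be 0.50 / 0.90 = 55.6% before the observed rate reached the 50% trigger.

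**The case against.** **The criterion covers the drugs described as being in ordinary use.** SP is described as replacing chloroquine as first-line drug (section III), and amodiaquine as regularly used in pregnancy in Kenya (section VIII.E). Exclusion 4 covers all three, and the urine test backs up the sulfa part. The sentence on quinine reports what agencies recommend, not what these clinic attendees take. This stands, and it is why f may be low.

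**A woman still parasitemic after a completed course was not cleared by it.** Her later clearance cannot simply be credited to that drug, and she may be harder to clear. A reader might infer that the gap always favours the finding that SP works. The documents do not support that. Understated failure is the usual direction, not a certain one.

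**Randomisation balances such women in expectation.** A reader might infer that the folic acid comparison is biased towards one arm. Nothing in the protocol suggests that; the effect on objective 1 is dilution.

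**Form 2 is not a clean benchmark.** Drug taken during follow-up acts directly on the outcome, whereas prior use comes before a confirmed positive smear. The same list also names a sensitive response as a reason for exclusion. It is therefore too strong to call the two rules a formal contradiction. They are better described as unequal treatment of similar contamination, to be reconciled.

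**The exposure is recorded and could be handled in analysis.** The analysis plan is not shown and may do so. But eligibility is set in the protocol, and removing the exposure at entry is simpler than adjusting for it later. This lowers the weight of the point without removing it.

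**Conclusion.** The gap in the text is real. The entry washout covers fewer drugs than the follow-up rule, no other criterion closes the difference, and the wider treatment history is collected but not used for eligibility.

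Its effect is probably small. With an assumed 2-10% of women affected and none of them able to fail, SP failure would be understated by 2-10% in relative terms. The folic acid contrast would shrink from 10 points to between 9.8 and 9.0, and power would drop from 82.6% to between 81.8% and 78.0%. These figures rest on an assumed share, on complete protection of that share for as long as failure is counted, and on equal shares in each arm. With less complete protection, failure would be understated by less, and the sign could reverse. The absolute failure rate and the 50% trigger are more exposed than the comparison of arms.

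This is a cheap improvement, not a threat to the trial's main comparison.

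**What to change.** Reconcile exclusion 4 in section VII.C with the first exclusion reason on the follow-up form by widening exclusion 4 to intake of sulfa-containing drugs or any antimalarial in the previous month. Apply it from the answers already recorded in item 11 of the screening form, so that the recorded history has a stated use.

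The change is one phrase and needs no new question, sample or data field. A few screened women become ineligible. For drugs other than sulfa compounds, the rule will rest on the woman's own report, as it already does for the 4-aminoquinolines, because the urine test does not detect them.

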**D. Outcome measures and sample size**

Outcome measures in the three arms will be the prevalence of parasitemia at day 2, 3, 7, 14, 21 and 28 following treatment with SP and change in hemoglobin level comparing day 0 (day of SP treatment) to day 28. In line with international criteria the following definitions are used (WHO 2003, see also Annex 5). Early Clinical Treatment Failure (ETF) will be defined as having at least one of the following: (a) the development of danger signs of severe malaria (see above under exclusion criteria 9) on day 1, 2, or 3 in the presence of parasitemia; (b) parasitemia on day 2 higher than the day 0 count; (c) parasitemia on day 3 in the presence of an axillary temperature of ≥ 37.5; or (d) parasitemia on day 3 ≥ 25% of the parasite count on day 0. Late Clinical Treatment Failure (LTF) will be defined as either the presence of parasitemia on any day from day 4 to 28 in the presence of an axillary temperature of ≥ 37.5, OR the development of danger signs after day 3, without previously meeting any of the criteria of ETF. Late parasitological failure is defined as the presence of parasitemia on any day from day 7 to 28, in the presence of an axillary temperature of < 37.5 without previously meeting any of the criteria of ETF or LTF.

A sample size of 600 women, 200 of whom receive SP and folic acid 5 mg, 200 of whom receive SP and folic acid 400 g and 200 of whom will receive SP and placebo folic acid for 2 weeks, will allow us to detect an increase from 5% to 15% parasitological failure rate at day 7, comparing the folic acid placebo arm with the folic acid 5 mg arm and the folic acid 400 g arm, with 80% power and 95% confidence, when taking 25% loss to follow up into account.

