***Follow up:*** Women will be asked to return on day 2, day 3, day 7, day 14, day 21, and day 28 (see annex 2). At these days the malaria smear will be repeated, and women will be questioned on complaints, side effects and medication use. They will be asked to bring the folic acid tablets (either folic acid 400 g, folic acid 5 mg or folic acid placebo) that are remaining to every clinic visit and a tablet count will be done to ensure compliance. Blood will be taken by finger stick for a malaria smear at every follow up date and in case of intercurrent visits. On day 2 or the first follow-up appointment made on a weekday, all clients will see the study counselor or study nurse to be informed about the HIV-test results of the study. At day 7 an additional 1 ml of blood will be taken for serum folate levels to assess adherence. At day 14 and 28, a hemoglobin measurement will be done. Women who do not return for follow up sampling will be visited at home to ask if they are still interested in participating. They will be encouraged to visit the clinic, or blood samples will be taken at home. If a woman develops early or late treatment failure or shows failure to clear parasites during follow up at day 7, day 14, or day 21, she will be treated with quinine, 600 mg three times daily for 7 days, according to the national guidelines. If a woman is parasitemic on day 28, she will receive her next dose of intermittent presumptive treatment with SP if there are no contra-indications (no history of side-effects), otherwise she will also receive quinine. During enrollment, the importance of ensuring their parasitemia is cleared with the alternative drug (quinine) and the need to adhere to their dosing regimen will be emphasized to women. In addition, they will be advised that quinine in therapeutic doses is felt to be safe to take during pregnancy. They will be informed about the potential side-effects of quinine, and advised that these side effects though unpleasant are almost always reversible. Thus, they will be told to continue the medication despite side effects but told to return to clinic for further consultation if they experience serious side effects or if they feel they cannot tolerate the side effects. Women who have a treatment failure on SP and who are treated with quinine will receive a follow-up appointment after 7 days to ensure clearance of parasitemia. Women who have parasitemia on day 7 after the initiation of quinine for SP treatment failure will be offered admission for supervised quinine intake, paid by the SP-folate study (because of the side-effects, many women may not adhere to quinine). Women who refuse admission for supervised quinine therapy will be offered the option of mefloquine treatment. A follow-up appointment after 1 week will be made to ensure clearance of parasitemia after either supervised quinine therapy or mefloquine therapy. If women do not show up for their post-treatment failure visits, they will be visited at home. Mefloquine is mentioned as an alternative drug that can be used for the treatment of malaria in pregnancy in the “Clinical guidelines for diagnosis and treatment of common conditions”, published by the government of Kenya (MOH Kenya 2002).

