**If yes, on any of the above complaints: refer to the CO or study physician**

1. Did you use any medicine between your last and the present visit? [_] 1=yes 2=no

If yes, what medicine did you use, and for how long?

_________________________________________________________________________

**8.** Blood smear: Result: [_] 1=positive 2=negative 9=not done

If positive for malaria: count [_][_][_][_][_] / 300 WBC

Species: [_]

1 = plasmodium falciparum

2 = plasmodium falciparum and malariae

3 = plasmodium malariae

4 = plasmodium ovale

5=other, specify__________________________________

**9.** Blood for folate serum levels taken on day 7: [_] 1=yes 2=no 8 = not applicable

If yes, place of storage in Kisian: ____________________________________________

**10.** Hemoglobin (only on day 14 and 28 or on request): Hb [_][_].[_] g/dl

**11.**  Additional history and examination: (Examining clinical officer or physician ____________)

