| **3** | **Danger signs in the presence of parasitemia** | **Treatment failure, exclude** |
| **4-6** | Parasitemia of 0 | Continue |
| **4-6** | Parasitemia and no danger signs and an axillary temperature < 37.5 ºC | Continue |
| **4-6** | **Parasitemia > 0 and an axillary temperature ≥ 37.5 ºC** | **Treatment failure, exclude** |
| **4-6** | **Danger signs in the presence of parasitemia** | **Treatment failure, exclude** |
| **7-28** | Parasitemia of 0 | Continue |
| **7-28** | **Any parasitemia**  **(either or not danger signs or an axillary temperature ≥ 37.5 ºC)** | **Treatment failure, exclude** |

**If treatment failure, treat with Quinine.** Make a check appointment for after one week.

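### No day-28 haemoglobin is planned for women who fail before day 28, and under the trial's own hypothesis that loss is larger in the folic acid arms

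*Protocol*

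**What the plan says.** **Objective and outcome.** Section VI, Objective 1, asks whether folic acid affects the efficacy of SP in clearing parasitaemia "and improving hemoglobin levels". Section VII.D sets the haemoglobin outcome, by arm, as "change in hemoglobin level comparing day 0 (day of SP treatment) to day 28".

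**Measurement.** Section VII.E, Follow up: "At day 14 and 28, a hemoglobin measurement will be done". Form 2, item 10, agrees: "Hemoglobin (only on day 14 and 28 or on request". Annex 2 adds a haemoglobin at intercurrent visits.

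**What happens at failure.** The staff table in Annex 5, meant for every participant's file, puts "Treatment failure, exclude" against each type of failure from day 1 to day 28. Its visit table offers only continue or stop at each visit. Form 2, item 14, lists resistance grades among the reasons for exclusion, for example "RIII resistance: -A parasite density at Day 3 that is > 25% of the Day 0 parasite density". It keeps these apart from the exit code "4) End of study after 28 days".

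**After failure.** Under Follow up, women treated with quinine "will receive a follow-up appointment after 7 days to ensure clearance of parasitemia". Women still parasitaemic then get further treatment and further weekly checks (also section VIII.E). No haemoglobin is named for any of these visits.

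**Against this.** Section VII.B says participating women are followed to 28 days after the start of treatment, and inclusion criterion 4 requires availability for the whole study period.

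**The concern.** Stopping at failure does little damage to the parasitological outcome, because the failure is already recorded. Haemoglobin change to day 28 is different: when a woman fails on day 3, 7 or 14, her day-28 value does not yet exist. If she then leaves the schedule, it is never taken.

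The women lost are not a random subset. The trial exists because folic acid may raise the failure rate, so under its own hypothesis more women go missing from the folic acid arms. The protocol also links infection to lower maternal haemoglobin (section IV) and expects SP treatment to reduce anaemia (section VIII.D), so the missing women are likely to be the worse haemoglobin responders. Part of the selection acts on haemoglobin directly. A haemoglobin below 7 g/dl is a danger sign in Annex 5, and a danger sign with parasitaemia is a failure.

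At stake is whether the trial can detect a haemoglobin cost of folic acid that works through treatment failure. A statistical analysis plan can model missing values, but it cannot recover measurements that were not taken.

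**Working it through.** **1. Is a day-28 value planned, by time of failure?**
- Failure before day 14: excluded under Annex 5. Neither the day-14 nor the day-28 haemoglobin is planned. A haemoglobin may exist if the failure was found at an intercurrent visit.
- Failure on day 14: that day's haemoglobin is scheduled, but no day-28 value.
- Failure on day 21: the post-quinine check falls on about day 28, but only parasite clearance is named for it.
- First parasitaemic on day 28: the haemoglobin is scheduled at that visit, so the outcome is observed.

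The gap therefore concerns women who fail before day 28.

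**2. The plan's own figure.** The only sample-size calculation is for day-7 parasitological failure, 5% v 15%, with 80% power, 95% confidence and 25% loss. With a two-sided alpha of 0.05 and a continuity correction it gives 160 per arm, and 160 × 1.25 = 200, the stated number. There is no calculation for haemoglobin. The result matters here only because it confirms that 5% and 15% are the protocol's working rates.

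**3. Women without a planned day-28 haemoglobin because of failure** (n × failure rate, n = 200 per arm)

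| Rates | Placebo arm | Folic acid arm |
|---|---|---|
| Protocol, day 7: 5% v 15% | 200 × 0.05 = 10 | 200 × 0.15 = 30 |
| Study in Gambian children, day 28: 21/131 = 16.0% v 22/73 = 30.1% | 200 × 0.160 = 32 | 200 × 0.301 ≈ 60 |

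The second row is an upper bound at those rates, because cumulative failure to day 28 includes failures first seen on day 28. The first row has no such dilution. If the 25% loss is independent of failure, 150 × 0.95 = 142.5 v 150 × 0.85 = 127.5 women would have the measurement in the first row, and 150 × 0.840 = 126 v 150 × 0.699 ≈ 105 in the second.

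**4. Harm that acts through failure and is not seen.** Assume failures have a haemoglobin change D g/dl worse than non-failures, and that non-failures change equally in both arms. The difference between the randomised arms is (f1 − f0) × D, where f1 and f0 are the failure rates with folic acid and placebo. The comparison among non-failures shows zero.
- 5% v 15%: 0.10 × 0.5 = 0.05 and 0.10 × 1.0 = 0.10 g/dl.
- 16.0% v 30.1%: 0.141 × 0.5 = 0.07 and 0.141 × 1.0 = 0.14 g/dl, again an upper bound.

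For scale, an assumed SD of 1.2 g/dl and 150 women per arm give a standard error of 1.2 × √(2/150) = 0.139 g/dl. The hidden difference is then about 0.4 to 1.0 standard errors (0.05/0.139 to 0.14/0.139).

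**5. Spurious advantage with no true haemoglobin effect.** Suppose a latent severity factor decides failure and has correlation ρ with a poorer haemoglobin change. The mean change among non-failures, in SD units, is ρ × φ(c)/(1 − f), with c the (1 − f) normal quantile.
- 5% v 15%: φ(c)/(1 − f) is 0.109 v 0.274, difference 0.166. For ρ = 0.2 to 0.5 this favours folic acid by 0.03 to 0.08 SD.
- 16.0% v 30.1%: 0.290 v 0.498, difference 0.208. For the same ρ, 0.04 to 0.10 SD.

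Under both sets of assumptions the error runs towards hiding a harm of folic acid.

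**The case against.** **The gap is partly inferred from silence.** No sentence says that failures get no day-28 haemoglobin. Form 2 allows one on request, Annex 2 lists one at intercurrent visits, and the post-quinine visits continue until parasites clear. This stands as a reason to describe the value as not planned rather than prohibited. It does not rescue the outcome, because none of these routes secures a value on day 28.

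**The exclusion wording sits in a form and an annex.** The Follow up text does not say that failures leave the study, and section VII.B points to 28 days for everyone. Form 2's exclusion reasons also include a category that covers women with negative smears from day 7 to day 14, so that list is not reliable evidence of who stops. This is fair, and it makes the matter a conflict between sections. But the Annex 5 table is the instruction in each participant's file, and it is unambiguous.

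**Stronger readings that the documents do not support.** A reader might infer that haemoglobin is measured only in women who never fail. That is wrong for failures first seen on day 28. A reader might also infer that failures are deliberately dropped from the haemoglobin analysis. Section VII.F covers only parasite failure, so no haemoglobin analysis set is stated, and that may be left to the statistical analysis plan. Finally, a reader might fault the use of a change score. Section VII.D names an outcome, not a model, and adjusting the change for baseline gives the same arm effect as adjusting the day-28 value, so the protocol fixes nothing wrongly there.

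**Conclusion.** The point holds in this limited form: the protocol defines a day-28 haemoglobin outcome, but its operational documents take women off the schedule at failure, so those who fail before day 28 have no planned value. Under the trial's hypothesis the loss differs by arm.

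The counts of 10 v 30 of 200 follow from the protocol's own rates. The counts of 32 v about 60 are upper bounds based on a study in children. The g/dl and SD figures rest on assumed links between failure and haemoglobin, since the documents give none. If haemoglobin recovers fully by day 28 after rescue, the hidden difference shrinks towards zero. The bias is modest on these assumptions, so the documents do not support a claim that the trial would certainly miss a haemoglobin penalty. But larger numbers would not remove the bias, and it widens as the gap in failure rates between arms widens. Section VII.F already contemplates overall failure reaching 50% at 14 days.

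**What to change.** Reconcile section VII.B with Annex 5 and Form 2 so that exclusion at failure ends only the counting of further parasitological endpoints, not study follow-up. Leave the treatment of failures and the post-quinine checks as they are.

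Add to section VII.E and Annex 2 a finger-stick haemoglobin on day 28 for every randomised woman, including failures. On Form 2, record failure separately from the end-of-follow-up code.

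State that haemoglobin is compared by randomised arm in all women regardless of rescue treatment (a treatment-policy comparison), with the non-failure subset as supporting analysis only.

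The cost is one or two extra haemoglobin visits per woman who fails. For a day-21 failure, the existing post-quinine check already falls on about day 28. Transport money and home visits are already provided for, and women agree at entry to be available for the whole period. The change has to be made before enrolment, or as early in it as possible, because the missing values cannot be obtained later.
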